### *Allocation*

The 12 sub-districts will be randomly assigned using a 1:1 allocation ratio to either the intervention or control group using a computer programme after baseline assessment, and the groups will be set up. The random sequence will be produced by an outside researcher working at the HIV Netherlands Australia Thailand Research Collaboration (HIV-NAT) who is not directly participating in the project. Following the gathering of baseline data, the project coordinator and co-investigator will contact participants via telephone to inform them of their allocation status, ensuring that participants are blinded to their status throughout the initial evaluation.

### *Blinding*

Blinding will not be possible for those who deliver the programme due to the involvement of facilitators and coaches; additionally, participants cannot be blinded to their allocation status after the initial assessment. In order to reduce the potential of contamination, participants will not be informed of the other participants allocation status. To prevent evaluation bias, participant allocation status will be blinded from data collectors as well as statisticians contributing to data analysis. When blinding is compromised, the Research Manager will be notified as soon as possible to consult with the research team for the most appropriate course of action.

Only in cases where a participant or a member of the research team reports experiencing serious harm as a result of taking part in the study will the unblinding of participants be permitted.

### *Training for facilitators and coaches*

The training of ParentChat facilitators will focus on the final version of the ParentChat Thailand Facilitator Manual. Trainers from the Philippines, where ParentChat has been implemented, will train the facilitators with the support of local trainers (Co-PIs [name], and [name]). Facilitators will be nurse practitioners and public health officers employed at Health Promotion Hospitals. The trainer from the Philippines will serve as a coach and will provide biweekly coaching sessions over Zoom.

The three-day training for facilitators and coaches will concentrate on developing the following abilities: 1) overview of the parenting skills and programme content; 2) managing parent groups; 3) using a collaborative approach to facilitation; and 4) managing logistics and technology. The training will take place in a hotel meeting facility or at the Boromarajonani College of Nursing, Udon Thani.

### *Programme delivery*

The 120 parents/primary caregivers in the intervention group will be divided into six groups of 20 participants who live in the same sub-districts. Each group will be overseen by one facilitator who will deliver the programme over nine weekly sessions. The group of six facilitators will receive weekly supervision from a trained coach during programme delivery.

Content for the adapted ParentChat programme include six core contents as following: 1) spending quality time with children; 2) talking with children to understand their feelings; 3) using praise and rewards to encourage positive behaviour; 4) establishing limits through effective instruction giving and consistent household rules; 5) nonviolent discipline strategies; and 6) problem solving with children.

Core activities during sessions will be delivered through LINE, a freeware application for instant communication. The programme will provide parents with activity assignments to complete with their children, including text/audio messages, illustrated comics, and videos. The facilitators will moderate text-based discussions around the parenting theme, support parents on an individual basis, and encourage them to apply the parenting skills at home. Parents will be prompted to give feedback regarding successes and challenges applying these parenting skills via audio or text messages during the week. When the next session begins, the facilitators will give a brief voice summary of the feedback and address possible solutions to a few key challenges. During implementation, participants will be supported with the necessary technical support, including IT support. Data bundles will be provided for internet access and to incentivise engagement.

### *Control condition*

The participants in the control group will be asked to join a LINE group in the same arrangement (20 per group) as those intervention group but they will not be any content or have any activity. There will be only general conversation among the group members. At the time of the intervention, the control will receive

standard care but not any active interventions. 'Standard care' includes access to Parent Schools in Mother and Child Health clinics at public hospitals, which are provided in all provinces and districts in Thailand.

## **C.2 Outcome data collection**

Data collectors with experience working at the community level with low-income families will be recruited and trained extensively by the study team on ethics, informed consent, and data collection procedures. A detailed protocol will guide data collection to ensure consistency across data collectors. Surveys will be translated into Thai by the researchers and back-translated by an independent translator to ensure accuracy.

Data collection during the trial will take place at four time points. In addition to baseline and one-month post-intervention assessment, which will be done in person, assessments during programme delivery will be conducted telephonically during weeks four, and eight. These assessments will assess changes in target outcomes over the past two weeks.

During pre-post assessments, data collectors will visit participants' homes to complete surveys with them on tablets. Data collectors will sit beside participants and go through the survey together. To reduce the potential for error, data collectors will enter participants' responses into the tablet while showing them the screen. For sensitive sections of the questionnaire (i.e., those relating to IPV and physical/emotional abuse), the tablet is given to the parent, who is able to complete it on their own, using earphones to listen to the questions by audio if they have difficulties with literacy. If parents would prefer to continue completing the survey with the data collector for the sensitive items (as opposed to using CASI), they will continue to use this approach.

## **C.3 Outcome and process evaluation measurements**

Summary of outcomes and process evaluation measurements are shown in Table 1. All measures will be translated into Thai language and back translated to check the accuracy of the translation.

### Sociodemographic information

Basic demographic questions about the parent/caregiver and the child will be asked using 25 items. Twenty three of these items are from those used in evaluations of PLH-YC in Thailand . These items include 1) parent/caregiver variables (eleven items): age, sex, gender, language, ethnicity, citizenship, religion, marital status, education level, basic literacy, and employment; 2) Child variables (three items): age, sex, school enrolment; 3) Child relationship variables (three item): the child's relationship to the caregiver; 4) household variables (six items): total monthly household income, other caregivers in the household, number of children in their care, biological parents, number of other adults in the household, and number of other children in the household. In addition, two items adapted from the Washington Group questions  on parent/caregiver and child disability will be asked whether they have any difficulties and, if so, what type of difficulty they have.

### Primary outcome

#### *1. Child maltreatment – physical abuse and emotional abuse*

Four items adapted from a reduced version of the International Society for the Prevention of Child Abuse and Neglect (ISPCAN) Child Abuse Screening Tool-Trial Parent version (ICAST-TP)  will be used to determine physical abuse and emotional abuse. The evaluation will be repeated four times consisting of the evaluation at baseline, post-test, and every four weeks during programme delivery. This study will evaluate the incidence of child abuse both in overall abuse by combining all subscales of two items assessing physical abuse and two items assessing emotional abuse. Participants report on the incidence of violent discipline use over the past four weeks using a frequency score of 0 to 8 or more times (e.g., how often did you discipline by spanking, slapping, or hitting with their hand over the past 4 weeks.).

### Proximal outcomes

#### *2. Positive parenting*

To evaluate positive parenting, five items adapted from the Alabama Parenting Questionnaire (APQ)  will be utilised at baseline, and post-test. We will also ask two of these questions at the fourth and eighth weeks during programme delivery for a total of four data collection points. Parents/caregivers will report on their behaviour from the previous two weeks. The two questions are, "how many times in the past 2 weeks did you play games or do other fun things with your child?" and "how many times in the past 2 weeks did you praise your child if he/she behaves well?" The items will be evaluated on a scale of 0 to 7, or 8 or more times, for frequency.

#### *3. Parenting stress*

To evaluate parenting stress, five items adapted from the Parental Stress Scale (PSS)  will be utilised at baseline, and post-test. We will also ask one of these questions at the fourth and eighth weeks during programme delivery for a total of four data collection points. The question asked about whether they disagree or agree with the statement, "The major source of stress in my life is my child(ren)." The items will be evaluated on a 5-point Likert scale of 0 to 4 (0 = strongly disagree; 4 = strongly agree).

### Secondary outcomes

#### *4. Attitude toward corporal punishment*

One item from the UNICEF Multiple Indicator Cluster Surveys (MICS): Child Discipline module  will be utilised to evaluate attitudes towards corporal punishment at baseline and post-test. Parents/caregivers will be asked whether they disagree or agree with the statement "In order to bring up, raise up, or educate a child properly, the child needs to be physically punished". Parents will report their attitude using a 5-point Likert scale of 0 to 4 (0 = strongly disagree; 4 = strongly agree).

#### *5. Child behaviour problems*

The Child and Adolescent Behaviour Inventory (CABI)  will be used to measure child behaviour problems, using a total of 14 items. The behaviour of the child over the previous two weeks will be reported by the parents/caregivers (0 = Not True; 2 = Very True). Problem behaviours will be assessed using the irritability subscale (4 items, for example, "has frequent mood changes") and the externalising subscale (10 items, for example, "often lies or cheats"). The items on both subscales are summed to produce a final score for child

behaviour problems. Additionally, two items modified from the Three Problem Scale-Parent Report  will be utilised to assess whether the specific concerns or issues change during an intervention. Parents will report whether the child's behaviour problems have occurred in the past two weeks and select the most problematic behaviour from a list of 10 and indicate how challenging the behaviour was on a scale of 0 to 8+ (0 = not a problem, 8+ = could not be worse).

#### *6. Parental mental health*

Parental mental health will be evaluated using the depression subscale of the Depression Anxiety Stress Scale 21 (DASS-21) . There are seven items in the depression subscale, such as "I felt down-hearted and sad." Parents will report their incidence of depressive symptoms during the past two weeks using a Likert scale (0 = Never; 3 = Always).

#### *7. Parent exposure to IPV and intimate partner coercion*

Utilising seven items from an adapted version of the WHO Violence Against Women Instrument (VAWI), which are part of the WHO Multi-Country Study Questionnaire on Women's Health and Life and Domestic Violence against Women , adults' self-reports of IPV and coercion over the past week will be evaluated. We separate the questions for men and women and ask them about experiencing and inflicting violence in compliance with WHO ethical and safety standards for intervention research on violence against women. Questions for men and women are segregated in accordance with WHO ethical and safety recommendations for intervention research on violence against women , and both will be asked about experiencing and perpetrating.

As a result, the questions are divided into two sections, the first consisting of five items and the second consisting of two items. Women will be questioned about their experiences as victims of violence in the first section, while men will be questioned about their experiences as perpetrators of violence. The items in this section include frequency of being respected ("my partner [I] respected my [my partner's] feelings in disagreement"), emotional violence ("my partner [I] insisted on knowing where I [my partner] was at all times"), financial autonomy restriction ("my partner [I] refused to give me [my partner] money for household expenses, even when my partner [I] had money for other things."), physical assault ("my partner [I] pushed, shoved, or slapped me [my partner]"), and psychological aggression ("my partner [I] insulted, shouted, yelled, or swore at me [my partner]"). The roles of men and women are reversed in the second section, with women being questioned about perpetrating acts of violence while men are the victims. The items in this section include the frequency of defending violence ("at a time that my partner [I] hit me [my partner], I [my partner] fight back physically") and partner mistreatment ("I [my partner] physically mistreated my partner [me] when my partner [I] was not physically mistreating me [my partner]"). All answers are coded on a frequency scale of 0 to 7, or 8 or more times. Please note that the squared brackets in the question examples refer to questions being asked to men.

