## **B.3. Objectives**

The objectives of this study are:

1. To evaluate the initial effects of ParentChat on the primary outcome of physical and emotional abuse, and the proximal outcomes of positive parenting and parenting stress at one-month post-intervention and at the fourth and eighth weeks during programme delivery.
2. To evaluate the initial effects of ParentChat on the secondary outcomes of attitudes to corporal punishment, child behaviour problems, parental mental health, parent exposure to intimate partner violence, child/Adolescent exposure to risks, online safety, child learning and development, and parent support of education at one-month post-intervention.
3. To test the feasibility of the Thai ParentChat system by assessing:
  - a. Implementation fidelity
  - b. Programme adherence
  - c. Participant satisfaction
  - d. Acceptability and feasibility

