To evaluate the hypothesis regarding measuring effectiveness on primary and secondary outcomes, two-tailed tests given a type I error of  $p(\alpha) < 0.05$  and power = 0.8 will be used. Along with the estimated values, 95% confidence intervals and p-values will be presented. Multilevel analysis (MLA) was used to analyse the results because the data is multilevel structured. The data from repeated measurements taken at different times makes up the lowest level. The second level is the individual level, and the third level is the level of sub-district. Primary and secondary outcomes that are on a frequency scale, including child maltreatment, positive parenting, parent exposure to IPV, child/adolescent exposure to risks, online safety, and child learning and development, which are discrete data, will be utilise distribution testes to determine whether to use a Poisson regression or a negative binomial regression if the data is overdispersion. For the ordinal scale outcomes, including parenting stress, attitudes toward corporal punishment, child behaviour problems, parental mental health, and parent support for education, we will use a linear regression to measure the differences between the two groups. A two-level model will be performed comparing post-intervention effects across all outcomes, controlling for baseline and the random effect will be the cluster, and participants ID. In addition, a three-level model will be performed comparing time trends across child maltreatment and proximal outcomes.

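### Parent exposure to IPV is carried as one seven-item frequency outcome, but its items mix violence experienced with the respondent's own violence, in opposite proportions for women and men

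*Protocol*

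**What the plan says.** Section B.3 of the protocol names the secondary outcome as "parent exposure to intimate partner violence", and hypothesis 3 in B.4 uses the same notion.

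Section C.3, outcome 7, builds it from seven items over the past week in two sections, "the first consisting of five items and the second consisting of two items". The roles are fixed by sex:

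- Section 1: "Women will be questioned about their experiences as victims of violence in the first section"; male respondents answer the same items as perpetrators.
- Section 2: the roles switch, "with women being questioned about perpetrating acts of violence while men are the victims".

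The same text says that "both will be asked about experiencing and perpetrating", so collecting both directions is deliberate. One of the five section-1 items is not violence: "The items in this section include frequency of being respected". One of the two section-2 items asks about fighting back on an occasion when the man hit the woman.

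Table 1 gives the outcome one row with seven items. Section C.4 lists it among the outcomes to be modelled by Poisson or negative binomial regression: "child maltreatment, positive parenting, parent exposure to IPV, child/adolescent exposure to risks, online safety, and child learning and development, which are discrete data". The protocol does not say whether the two sections are scored together or apart.

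**The concern.** The label and the content do not match. A man's section-1 answers describe what he did to his partner, and a woman's section-2 answers describe what she did to hers. Neither is that respondent's exposure to violence, yet both sit inside the single outcome tested for objective 2.

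Two errors of interpretation could follow if the items are pooled. A real fall in violence experienced would be diluted by perpetration items that did not move. A fall in admitted perpetration alone would be reported as parents being exposed to less partner violence. The second matters here because the answers are self-reported and, by the Blinding section, participants know their allocation after the first assessment. Intervention parents may become less willing to admit their own violence.

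**Working it through.** **Plan's own figures.** The protocol states no effect size, power or event rate for this outcome. The only figures to check are the item counts, and 5 + 2 = 7 agrees with Table 1.

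**Direction of the items (C.3, outcome 7).**

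| Items | Women answer about | Men answer about |
|---|---|---|
| Section 1, respect (1) | not violence | not violence |
| Section 1, violent or coercive (4) | violence experienced | own acts |
| Section 2, fighting back (1) | own act, but presupposes being hit | partner's act, but presupposes his own hitting |
| Section 2, mistreating partner (1) | own act | violence experienced |

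Without the respect item, women have 4 items experienced and 2 on their own acts, and men have 2 experienced and 4 on their own acts. Without the ambiguous fighting-back item as well, women have 4 and 1, and men have 1 and 4.

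**Illustration of size, if the items are pooled.** All inputs here are assumptions, because the protocol gives none of them:

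- The respect and fighting-back items are excluded.
- Each section-1 item has mean 1, and the section-2 item has mean r, with r from 0.25 to 1.
- Item means are the same for both sexes.
- The male share of respondents is p, from 0.05 to 0.30.

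Expected count experienced = 4(1 − p) + rp.
Expected count perpetrated = r(1 − p) + 4p.
Total = 4 + r.
Own-violence share s = [r(1 − p) + 4p] / (4 + r).

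If exposure truly changes by a ratio of 0.70 and perpetration does not change, the pooled ratio is 0.70(1 − s) + s = 0.70 + 0.30s. If exposure does not change and reported perpetration changes by 0.70, it is 1 − 0.30s.

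| p | r | s | Exposure alone at 0.70 appears as | Perpetration alone at 0.70 appears as |
|---|---|---|---|---|
| 0.05 | 0.25 | 0.4375/4.25 = 0.10 | 0.73 | 0.97 |
| 0.05 | 1 | 1.15/5 = 0.23 | 0.77 | 0.93 |
| 0.30 | 0.25 | 1.375/4.25 = 0.32 | 0.80 | 0.90 |
| 0.30 | 1 | 1.90/5 = 0.38 | 0.81 | 0.89 |

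**Sensitivity.**

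- With fighting back counted as the woman's own act, s = [2r(1 − p) + 4p] / (4 + 2r). This runs from 0.675/4.5 = 0.15 to 2.6/6 = 0.43.
- With no men at all and fighting back excluded, s = r/(4 + r), from 0.25/4.25 = 0.06 to 1/5 = 0.20. The problem shrinks but remains.
- By sex, with r = 1 and perpetration alone at 0.70, the women's total falls to (4 + 0.70)/5 = 0.94 and the men's to (1 + 4 × 0.70)/5 = 0.76. The same behavioural change therefore gives different apparent exposure effects in the two sexes.

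**The case against.** The strongest reply is that the protocol never says the seven items are summed. It does state a sum for the child behaviour inventory and has no such sentence here. Section C.4 lists outcomes mainly to assign a model family, and one row in Table 1 need not mean one score, since the child behaviour row holds two instruments. A statistical analysis plan that is not shown could score the sections apart. This stands in part: the numerical bias depends on pooling. It does not remove the mismatch, because the objective, the table and the analysis section all carry one outcome called exposure. No reading turns a man's report of his own acts into his exposure.

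A second reply is that section 1 always concerns the man's conduct and section 2 the woman's, whoever answers, so the items line up across the sexes as a measure of violence within the couple. That is fair if partners are of opposite sex, as the item wording supposes. It supports a couple-level outcome under that name, not one called exposure.

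A reader might go further in three ways that the text does not support.

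- That five of the seven items are a man's own violence: five are in the perpetrator role, but one is respect for the partner's feelings, so four are violent or coercive.
- That the fighting-back item is plainly perpetration, or counts one episode twice: being hit and hitting back are different acts, and the item carries information on both.
- That a false exposure effect is certain: this depends on pooling and on how perpetration reports change.

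Section D.3 also exempts men whose spouse takes part, which may lower the male share. Finally, this is one of eight secondary outcomes in a phase II trial, and the sample size does not depend on it.

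**Conclusion.** The concern holds as a mismatch between the objective and the outcome as listed. Parent exposure to IPV is one seven-item frequency outcome whose items mix experienced and committed violence in opposite proportions by sex.

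The consequence for the estimate is conditional on pooling, which the single row and single modelled outcome imply but no sentence states. Under the assumed male share and item frequencies, 10–38% of the count would be the respondent's own violence. A true exposure ratio of 0.70 would appear as about 0.73–0.81, and a change in perpetration alone of 0.70 would appear as an exposure ratio of about 0.89–0.97. These figures show direction and rough size only; nothing here shows that 240 participants in 12 clusters would detect the smaller ratios. The point should be corrected before analysis, but it does not touch the primary outcome.

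**What to change.** In section C.3 (outcome 7), Table 1 and section C.4, define two scores from the answers already planned:

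1. **IPV experienced**: women's four violent or coercive section-1 items, and men's section-2 mistreatment item. Use this for objective 2 and hypothesis 3. Because the item sets differ, report it by sex, or let the women's section-1 violence items lead.
2. **IPV perpetrated**: men's four violent or coercive section-1 items, and women's section-2 mistreatment item. Report it as a separate outcome.

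Report the fighting-back item descriptively and put it in neither score. Keep the respect item out of both violence counts and state how it is handled.

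If a combined score is preferred, rename it as violence within the couple and do not interpret it as exposure.

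The cost is wording in three places and one additional model, with no new items, visits or participants. The real drawback is fewer items and sparser counts over a one-week recall. This is worst for men, who would have a single experienced item, so their result may be descriptive only.
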